**Methods:**

We will conduct a two-arm, parallel group, stratified cluster randomized controlled trial of the NUrse-led COntinuum of care for people with Diabetes (*N*_1_ = 200) and prediabetes (*N*_2_ = 1036) (NUCOD) program, with primary care centers (9 outreach centers and 17 government health posts) as a unit of randomization. The NUCOD program will be delivered through the trained diabetes nurses in the community to the intervention group and the outcomes will be compared with the usual treatment group at 6 and 12 months of the intervention. The primary outcome will be the change in glycated hemoglobin (HbA1c) level among diabetes individuals and progression to type 2 diabetes among prediabetes individuals, and implementation outcomes measured using the RE-AIM (reach, effectiveness, adoption, implementation and maintenance) framework. Outcomes will be analyzed on an intention-to-treat basis.

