The Dhulikhel Hospital (DH) system is a community-oriented, nongovernmental health system with an extensive network of 21 rural community-based outreach centers. The DH system provides a well-suited setting for innovating a continuum of care for people with diabetes. In this trial, we aim to develop and implement a “continuum of care” program with trained nurses as the nucleus. The nurses, along with the community health worker, will coordinate and implement a composite of the DCP-3-recommended individual intervention components for the low-income setting: leading community awareness campaigns; organizing diabetes screening events; linking diabetic patients to comprehensive clinical care (which will have been structured based on standard guidelines); and ensuring treatment adherence and self-management through regular community-based group counseling programs. The primary objective of this study is to examine the effectiveness of this comprehensive intervention in promoting the health of the people with diabetes and prediabetes, and the secondary objective is to examine whether the nurse coordination will promote the implementation of the evidence-based, DCP-3-recommended interventions. We hypothesize that the NUrse-led COntinuum of care for people with Diabetes and prediabetes (NUCOD) program will improve both clinical outcomes as well as implementation outcomes, compared with diabetes usual care in low-income settings.

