### Outcome measures

We will examine both clinical outcomes and implementation outcomes as we hypothesize that the nurse-led continuum of care program will improve both health and the implementation of priority interventions in diabetes. The outcome measure will pertain to the individual participant level. The primary outcome for the diabetes group is the HbA1c level at 12 months from the intervention. The HbA1c level is indicative of the average level of blood glucose over the past 2–3 months [22]. The primary outcome for the prediabetes group is the incidence of diabetes at 12 months from the intervention.

The secondary outcomes are blood pressure, body mass index (BMI) and lipid levels. Also, the secondary outcomes include a series of implementation outcomes in the RE-AIM (reach, effectiveness, adoption, implementation, and maintenance) implementation framework [23–25]. We provide details on those measures in the following (see Table 2 for a summary).

**Table 2 Tab2:** Measures of outcome variables

	Assessment method	Assessor	Baseline	Midline (6 months)	End line (12 months)	Variable

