Descriptive statistics (i.e., counts, means and proportions) will be calculated to evaluate the reach, effectiveness, adoption and implementation of the program.

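### The plan hypothesises better implementation outcomes than usual care, but assigns reach, adoption and implementation descriptive statistics and no cluster-adjusted arm comparison

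*Protocol article*

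**What the plan says.** The Background sets a question about cause: "the secondary objective is to examine whether the nurse coordination will promote the implementation of the evidence-based, DCP-3-recommended interventions". It then hypothesises that the program "will improve both clinical outcomes as well as implementation outcomes, compared with diabetes usual care in low-income settings". The Outcome measures section repeats this: "we hypothesize that the nurse-led continuum of care program will improve both health and the implementation of priority interventions in diabetes".

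The status of these outcomes is given in two ways. The Outcome measures section says "the secondary outcomes include a series of implementation outcomes in the RE-AIM" framework. In the abstract, the sentence that lists the primary outcome ends with "and implementation outcomes measured using the RE-AIM (reach, effectiveness, adoption, implementation and maintenance) framework".

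For analysis, the closing sentence of the Statistical analysis section reads: "Descriptive statistics (i.e., counts, means and proportions) will be calculated to evaluate the reach, effectiveness, adoption and implementation of the program". Before it, that section describes GEEs clustered by site with an exchangeable correlation and robust variances. It applies them to HbA1c at 6 and 12 months and to diabetes incidence in the prediabetes group. Mixed models are named for the same two outcomes in subgroups.

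**The concern.** A hypothesis of improvement over usual care needs a contrast between arms with a measure of uncertainty. Counts, means and proportions give neither. In a trial that randomizes 26 health centers, the uncertainty must also reflect the clustering. If the plan is followed as written, readers would compare arm summaries by eye, and any statement that the program did or did not improve implementation would have no estimate behind it. The Discussion presents implementation effectiveness as evidence for policy-makers, so this objective is not incidental.

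**Working it through.** No stated figure is in dispute. The check sets the objective, the outcome definitions and the analysis text side by side.

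**1. What each implementation outcome is, and what analysis is named for it**

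| Outcome (Table 2, Implementation outcomes section) | Level and timing | Analysis named |
|---|---|---|
| Reach | Participants divided by those eligible; 6 and 12 months | Descriptive |
| Effectiveness | Equated with the clinical outcomes | Descriptive, but HbA1c and diabetes incidence also by GEE |
| Adoption, patient level (SDSCA, with DTSQ) | Individual; baseline, 6 and 12 months | Descriptive |
| Adoption, clinic level | Share of approached clinics that joined; not an arm contrast | Descriptive |
| Implementation (fidelity) | Checklist by standardized patients; 6 and 12 months | Descriptive |
| Glucose self-monitoring, medication adherence | Individual, self-reported; 6 and 12 months | None by name; descriptive if counted under a RE-AIM dimension |

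Only effectiveness has an inferential analysis. The general GEE sentence speaks of assessing the program effect and names no outcome, but the sentence after it applies the model to HbA1c. The implementation outcomes are then handled separately.

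**2. Is an arm comparison feasible?**

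The Sample size section gives 91 (diabetes) and 471 (prediabetes) per arm before the dropout allowance, both derived from clinical outcomes. They are taken here as given, as approximate 12-month numbers. With 26 clusters, the mean cluster size is m = 182/26 = 7.0 and 942/26 = 36.2. The protocol gives cv = 0.25 and ICC = 0.01. The upper ICC of 0.10 and all response rates below are assumptions. The protocol does not say which cohort completes each self-report item, so both are shown.

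- Design effect: DE = 1 + [(1 + cv²)m − 1] × ICC
- Effective size per arm: n_eff = n / DE
- 95% half-width with both proportions at 50%: 1.96 × √(0.5 / n_eff)
- Power: Φ{[|p₁ − p₂|√n_eff − 1.96√(2p̄(1 − p̄))] / √[p₁(1 − p₁) + p₂(1 − p₂)]}

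| n per arm | ICC | DE | n_eff | Half-width | Power |
|---|---|---|---|---|---|
| 91 | 0.01 | 1.06 | 85.5 | 15.0 points | 77% (50% vs 70%) |
| 91 | 0.10 | 1.64 | 55.4 | 18.6 points | 58% (50% vs 70%) |
| 471 | 0.01 | 1.37 | 342.6 | 7.5 points | 98% (50% vs 65%) |
| 471 | 0.10 | 4.75 | 99.2 | 13.9 points | 57% (50% vs 65%) |

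Worked line, diabetes at ICC 0.01: DE = 1 + (1.0625 × 7 − 1) × 0.01 = 1.064; n_eff = 91/1.064 = 85.5; half-width = 1.96 × √(0.5/85.5) = 0.150.

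The normal approximation ignores the limited number of clusters, so these values are slightly favourable. They show that an estimate would be informative, though imprecise in the smaller cohort.

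**3. Status of the outcomes**

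The Background (secondary objective), the Outcome measures section (secondary outcomes), Table 2 (only HbA1c and diabetes incidence under the primary heading) and the Sample size section (sized on those two) all agree. The abstract alone places implementation outcomes with the primary outcome.

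**The case against.** The best defence is that the descriptive sentence does not claim to be exclusive. It lists effectiveness, yet HbA1c and diabetes incidence are plainly tested. The GEE paragraph opens in general terms, all analyses are said to be two-sided, and the abstract says outcomes will be compared with the usual treatment group. Blood pressure, BMI and lipids have no model of their own either, which suggests an article that condenses its secondary analyses and leaves them to a fuller plan.

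Part of this stands. Effectiveness must be excepted, and silence about the other secondary clinical outcomes is no finding. For reach, adoption and implementation, however, the article is not silent: it names a method, and that method does not answer the stated hypothesis. The overlap for effectiveness supplies no comparison for adoption, self-monitoring or medication adherence.

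Several stronger readings are tempting but unsupported:

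- *The objective cannot be tested.* The outcomes are defined for individual participants in a two-arm trial, and nothing forbids a comparison. The plan simply does not provide one.
- *Clustering would be ignored and precision overstated.* The plan proposes no unclustered test of these outcomes, so there is no such error to measure.
- *Table 2 is wrong to type the SDSCA as binary.* Patient-level adoption is defined as the share of people adherent to advice, which is binary. No cut-point is given, so no particular loss of information can be stated. The doubt is confined to the DTSQ, which shares the table row but is described as the patient's perception of treatment.
- *The confirmatory set is unclear for these outcomes.* Four places in the body agree that they are not primary, so the abstract is a wording slip.

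**Conclusion.** The point holds in a limited form. The protocol states a comparative hypothesis for implementation outcomes, but for reach, adoption and implementation it fixes only descriptive statistics, and it names no arm comparison for the self-reported items. As written, it yields no cluster-adjusted effect estimate for its secondary objective, apart from the effectiveness dimension. The two primary clinical analyses are not affected.

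The conclusion rests on reading the text as it stands and needs no numerical assumption. The precision and power figures are illustrative and depend on the assumed rates and the assumed ICC range. They support only the statement that a comparison is worth making and is not powered by design. The change is worth making before analysis, because a declared objective depends on it.

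**What to change.** Choose one of two routes.

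1. **Add the comparison.** For the patient-level implementation outcomes collected in both arms (SDSCA-based adherence, DTSQ, medication adherence, glucose self-monitoring), estimate the 12-month difference between arms with the planned GEE clustered by site. Adjust for stratum (outreach center or health post) and for the baseline value where it is collected, which per Table 2 means SDSCA and DTSQ only. Report each estimate with a 95% CI and label it a secondary comparison, not powered by design. Analyse the DTSQ as a score and amend its entry in Table 2. State that fidelity and clinic-level adoption remain descriptive, and mark reach explicitly as well.
2. **Or narrow the claim.** Reword the secondary objective, and the hypothesis in the Background and the Outcome measures section, as descriptive for implementation outcomes.

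Under either route, correct the abstract so that implementation outcomes are secondary, as in the Outcome measures section.

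The cost is a few sentences and, under the first route, a few extra models. No new data, visits or participants are needed.

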#### Economic analysis

Cost-effectiveness analysis will also be conducted with a Markov simulation model to be developed. The Markov model has been widely used to describe the development of the chronic noncommunicable diseases [42]. All direct costs (e.g., screening cost, cost of training of nurses and cost of EHR system development) and indirect costs will be collected. All costs will be reported in 2020 US dollars using the exchange rate of 1 USD = 111.7 NPR. We will solve the model numerically over a short and long timeframe (i.e., 10 years and 20 years), and calculate the incidence of diabetes, costs and quality-adjusted-life-years (QALYs) under the control case or the NUCOD program. Incremental QALY and costs of the NUCOD program relative to the control case will be calculated with an annual discount rate of 3%. We will use WHO-CHOICE (Choosing Interventions that are Cost-Effective) thresholds for cost-effectiveness: an intervention is defined as “cost-effective” if it produces a healthy life year for less than three times the gross domestic product (GDP) per capita, and as “very cost-effective” if it produces a healthy life year for less than the GDP per capita [43, 44].

### Data monitoring and quality assurance

The trial will receive overall supervision from a Trial Steering Committee (TSC) who will conduct quarterly on-site monitoring of health clinics (with repeat visits to sites where performance is a concern), monitor trial progress and review the quality and completeness of data. The TSC will include an independent chairperson not involved directly with the study, one clinical and one methodological expert who are also not involved with the study, and a principal investigator of the study. Our trained diabetes nurses will be responsible for all aspects of local organization, such as identifying and recruiting participants, and RAs will be responsible for obtaining informed consent. A formal data monitoring committee (DMC) was not considered for the conduct of this study as this will be a low-risk intervention; however, the trial will be reviewed by national (every 6-month) and institutional (every 2-month) Ethics Committee Review Board members throughout the trial period. A Stakeholder and Public Involvement Group (SPIG) was also not formed as the study will be mainly led by the trained diabetes nurses.

## Discussion

To our knowledge, this study is the first to include a sizable number of diabetes and prediabetes participants in a community-based setting and a continuum of care program run by diabetes nurses. The priority health problems of the target population, the potential solution of the problem, recruitment strategies and intervention delivery formats were discussed early on by the study-specific collaborative partners in DH and the community, which will lead to the success of the program.

The results of this study may provide much-needed evidence for the policy-makers on the clinical effectiveness, cost-effectiveness and implementation effectiveness of nurse-led continuum of care for people with diabetes and prediabetes in resource-limited settings. Many low-income countries now face a double burden of chronic diseases and infectious diseases. But large trials have been rarely conducted in those settings in low-income countries. This proposal has several unique features. First, although nurse-led diabetes prevention and management programs have been tested earlier in different settings, this is unique because it addresses the full continuum of care from the level of awareness and detection to management and follow-up all led by nurses. Second, the study focuses not only on clinical outcomes but also on implementation outcomes. The nurse-led continuum of care may theoretically improve health among people with diabetes but also improve adoption of DCT-3-recommended and evidence-based individual intervention elements. We will also use some innovative strategies to assess program implementation fidelity and quality, such as the use of standardized patients. Third, the study builds a culturally tailored and locally contextual training program for nurses utilizing the existing training programs of the International Diabetes Federation and the American Diabetes Association. Fourth, the study utilizes a unique setting of suburban tertiary-level community-based health institutions that have an extensive network of health centers in rural areas as well. Hence, the experience we gain from this project will be easily translated into larger health care systems. Fifth, we have designed the trial, taking implementation, feasibility and sustainability into full consideration. For instance, we did not offer free care to all program participants in the trial as that will not be sustainable once the program stops.

Although this trial may hold promise for better clinical and implementation outcomes, it is not without potential limitations. We will have a large sample size, but the setting of the study may not represent the entire nation, thus limiting the generalizability of our findings. However, our setting will cover both public and private health sectors and may serve as a proxy for the Nepalese population.

## Trial status

The protocol is the first version as we have not changed any information after registering in the ClinicalTrials.gov registry on 18 October 2019. We have not yet started the recruitment of our sample. The approximate date when recruitment will be completed will be the end of December 2020.

## Data Availability

The proposed project is a collaborative effort between investigators at SYSU and KU. The aforementioned institutions will jointly share ownership of the data. Study investigators at SYSU and KU will have access to the data. Data can be obtained from the corresponding author upon reasonable request.

## Abbreviations

ADA: American Diabetes Association
BMI: Body mass index
DCP-3: Disease Control Priority-3
DH: Dhulikhel Hospital
DPP: Diabetes Prevention Program
DRT: Diabetes Risk Test
EHR: Electronic health record
FCHV: Female community health volunteer
HDL: High-density lipoprotein
ICC: Intraclass correlation coefficient
IDRS: Indian Diabetes Risk Score
ITT: Intention to treat
LDL: Low-density lipoprotein
MET: Metabolic equivalent of task
NPR: Nepalese Rupee
QALY: Quality-adjusted life years
QC: Quality control
USD: US Dollar
